## Abstract

**Background:**

Chronic non-specific neck pain (CNNP) is a prevalent musculoskeletal disorder known for its significant disability and economic burden, ranking second only to low back pain in musculoskeletal conditions. Physical therapy offers effective interventions for CNNP, including low-level laser therapy (LLLT). High-intensity laser therapy (HILT) is a recent treatment for musculoskeletal pain, but studies that support its use in CNNP are limited. The objective of this study is to assess the effect of high-intensity laser therapy on pain intensity in patients with CNNP, given the existing evidence on LLLT for this condition.

**Methods:**

This is a 2-arm, randomized, placebo-controlled trial with blinded evaluators. The research will be carried out in the laboratory of physical agents at the Andrés Bello University, Campus Casona de las Condes. Eligible participants include the entire internal and external community associated with Andrés Bello University suffering from chronic non-specific NP. Participants will be stratified by sex (4 subgroups) and randomized into 2 study groups: group 1 (HILT and stretching exercises) and group 2 (sham HILT and stretching exercises). Treatments will be performed twice a week for 4 weeks with 3 assessments: before treatment (T0), at the end of treatment (T1), and 12 weeks after treatment (follow-up) (T2). The main outcomes will be pain intensity at rest, pain intensity at movement (active cervical movements: flexion, extension, right and left side bending, and right and left rotation), and pain pressure threshold (average obtained for six evaluation points). Secondary outcome measures will include neck range of motion in the sagittal, coronal, and transverse planes and neck disability.

**Discussion:**

In this study, HILT’s effects on patients with non-specific NP will be compared to those of a sham laser intervention. This RCT will offer new evidence regarding the potential benefits of HILT in terms of pain intensity, range of movement, and disability in people suffering with non-specific NP.

**Trial registration:**

ClinicalTrials.gov NCT05689788. January 19, 2023.

## Introduction

### Background and rationale {6a}

Neck pain, a multifactorial musculoskeletal disorder, is the fourth leading cause of disability in adults, with a 30% annual prevalence [1, 2]. Individuals from developed countries, urban dwellers, and individuals engaged in office or computer work are more affected [3]. Neck pain is linked to sedentary habits, smoking, and psychological risk factors. Although it often resolves on its own or responds to treatment, 30 to 50% of patients may experience chronic pain [1, 2, 4, 5].

Neck pain is classified based on its duration (acute or chronic) and its mechanism (nociceptive, neuropathic, or nociplastic), depending on its association with the nervous system [1, 6]. Additionally, it is categorized as specific or non-specific based on its underlying cause [6]. Specific neck pain is associated to structural conditions such as radiculopathies, myelopathies, fractures, and joint inflammation. In contrast, chronic non-specific neck pain (CNNP) is often idiopathic and lacks identifiable structural injury [5, 6].

CNNP has a prevalence of around 50%, and its increasing occurrence among adolescents underscores the need for early intervention and preventive measures [4]. CNNP is associated with functional limitations, increased healthcare utilization, and frequent use of medication for pain relief [4]. As a public health concern, it leads to high socioeconomic costs, primarily due to job absenteeism. CNNP is linked to central sensitization, whose influence is important in conditions such as cervical myalgia or fibromyalgia [7]. CNNP can manifest as local or referred pain, hyperalgesia, reduced cervical mobility, and muscle tension. Additionally, cases of neuropathic pain may involve accompanying symptoms such as headaches, numbness, weakness, or tingling, with or without radiation to the upper limb [1, 3, 6]. CNNP medical treatments prioritize pain management using NSAIDs, opioids, or muscle relaxants, showing efficacy in acute NP cases [1, 8]. Other approaches include local injections of lidocaine or corticosteroids near nerve roots, zygapophysial joints, or cervical muscles, but evidence is inconclusive. Surgery is less common, reserved for radiculopathies or spinal cord compressions, with better short-term results compared to long-term [1, 8].

Laser therapy is widely used in physical therapy for tissue repair, wound healing, and pain reduction in musculoskeletal conditions [9, 10]. Its analgesic effects are associated with its ability to modulate the inflammatory process, release endogenous opioid peptides (β-endorphins), and decrease nerve conduction velocity, especially at higher potencies [9–12].

Laser radiation, present in the visible red and infrared light spectrum, varies in its biological penetration depth [12]. Laser production involves exciting atoms in a medium with free electrons, resulting in the emission of photons through stimulated radiation emission [11, 12]. These photons are absorbed by specific chromophores in tissues, such as water molecules, hemoglobin, melanin, and cytochrome c oxidase [11, 13, 14].

Laser therapeutic devices are categorized into two types: class IIIb, or low-level laser therapy (LLLT), and class IV, or high-intensity laser therapy (HILT), based on their emission power (less than or greater than 0.5 W, respectively) [15–17]. LLLT has athermal and superficial effects (3–4 cm) and is known for its photobiological effects (photobiomodulation) that stimulate or inhibit biological processes depending on the delivered energy dose (Arndt-Schultz law) [11]. In recent years, HILT has emerged as a novel approach for managing musculoskeletal pain, distinguished by its photothermal and photochemical effects [11, 13, 18]. With its higher power, HILT can deliver more energy to deep tissues, reaching greater depths owing to its infrared spectrum wavelengths (averaging depths of 10–12 cm) [18]. HILT offers distinct advantages over LLLT as it enables the delivery of higher energy over time. HILT allows for more energy deposition in deep tissues, resulting in both the biological effects of LLLT and thermal effects [13, 14, 18].

Currently, LLLT is widely recognized in physiotherapy as an effective resource for managing both acute and chronic neck pain and recommended by evidence-based guidelines [11, 15–17]. LLLT delivers immediate pain relief for acute neck pain and exhibits sustained effectiveness for up to 22 weeks post-treatment in chronic neck pain patients [10]. In contrast, HILT is being used for the management of musculoskeletal pain, reporting analgesic benefits and less disability in conditions such as osteoarthritis, epicondylalgia, and low back pain [15, 19–22]. Studies on the benefits of LLLT and HILT for musculoskeletal pain offer a basis for exploring class IV laser as a treatment for CNNP, building on the existing evidence on LLLT for this condition. However, there is limited evidence supporting HILT efficacy in the management of CNNP, with only a few studies available [6, 16].

### Objectives {7}

The main purpose of the research is to investigate whether pain intensity will decrease after HILT treatment compared with sham HILT after treatment and with a 3-month follow-up. Additionally, secondary outcomes such as changes in pain pressure threshold, active cervical range of motion (flexion, extension, left- and right-side bending, and left and right rotation), and cervical disability will be evaluated. The hypothesis of the study is that HILT will lead to greater pain intensity improvement than conventional treatment. The purpose of this article is to describe the methods and statistical analysis of this study so that this information can be made public.

### Trial design {8}

This is a 2-arm randomized placebo-controlled superiority trial (RCT) with patient and evaluator blinded to the group allocation. This study is reported in accordance with established clinical trial reporting standards: the Consolidated Standards of Trial Reporting (CONSORT). The protocol was developed following the recommendations of Standard Protocol Elements: Recommendations for Interventional Trials (SPIRIT).

The study has been approved by the Ethics Committee of the Eastern Metropolitan Health Service (SSMO), Santiago de Chile, following the Helsinki principles (approval date: October 26, 2022. N° 20200234) [23].

## Methods: participants, interventions, and outcomes

### Study setting {9}

The research will be carried out in the physical agent’s research and intervention laboratory of the Physical Therapy Career program at Andrés Bello University, Santiago de Chile. The protocol of this study has been registered in the Clinical Trials platform (http://clinicaltrials.gov), a resource provided by the US National Library of Medicine (ClinicalTrials.gov Identifier: NCT05689788).

### Eligibility criteria {10}

Participants in this study will be people of the internal and external communities associated with Andrés Bello University. Participants will be recruited through mailings and posters and will be contacted via email or telephone to schedule an in-person meeting at the laboratory. The evaluators will verify whether the patients will be eligible to participate in the study based on patient history and clinical examination.

The inclusion criteria are as follows:Participants must be at least 18 years old.Participants of both sexes.CNNP, defined as pain or discomfort in the cervical region between the superior nuchal line and the spinous process of T1 or the shoulder girdle, with the following criteria: NP in the last 3 months or more; a questionnaire score of cervical disability (NDI) equal to or greater than 5; and NP at rest of 3 or greater on a 0 to 10 numerical pain rating scale (NPRS) [3, 24].

The exclusion criteria are as follows [11]:Neck or shoulder musculoskeletal injuries in the last 3 months (fractures, sprains, tendinopathies, dislocations, or muscle tears).Osteosynthesis materials close to the shoulders, neck, or surrounding areas.Wounds or skin changes in the shoulder and/or neck region (such as psoriasis, scars, or burns).Analgesic, anti-inflammatory, or muscle relaxant drugs (either for continuous use or those used during the study).Neurological alterations such as paresthesia, loss of sensation (partial or complete), decrease in strength, and color changes in the neck, arms, forearms, or hands.Photosensitivity diagnosis.Skin phototypes V and VI (Fitzpatrick scale).Presence of solar urticaria or adverse reactions to sunlight.Presence of dermatomyositis, systemic lupus erythematosus, hepatic porphyria, cutaneous carcinoid syndrome, or pellagra.Cancer or tumors of some type have been diagnosed in the last 5 years.Epilepsy.

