### Criteria for discontinuing or modifying allocated interventions {11b}

There will be no changes in assignments, nor will migration of individuals between groups be allowed. If people discontinue treatment, the analysis will be by “intention to treat,” recording the reasons for leaving the study.

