### Relevant concomitant care permitted or prohibited during the trial {11d}

During the experiment, concurrent treatments such as chronic diabetes, hypertension, anxiolytics, and antidepressant drugs will be accepted. Throughout the course of the trial, participants will not be allowed to start any other interventions or medications, especially on the days that the evaluations and treatments are carried out.

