### Provisions for post-trial care {30}

During the initial evaluation session, participants will be given a document outlining all the considerations that should be made during the study period. The principal researcher will provide participants with his phone number, the researchers’ email addresses, and contact information about the physical therapy department at Andrés Bello University. The evaluators will keep an electronic record (in Microsoft Excel) of the medications taken during the week. In general, the treatments are safe and do not pose risks for the participants. However, if the individual exhibits any negative effects, they will be referred to the university health center for evaluation and treatment.

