### Outcomes {12}

The main outcomes will be the changes in pain intensity at rest (RPI), pain intensity at movement when performing active cervical movements in the sagittal (flexion–extension), coronal planes (neck right and left side bending) and transverse plane (right and left rotation) (MPI), and pressure pain threshold obtained as a mean of six points of the cervical spine and shoulder region according to the protocol of Rampazo et al. (Fig. 3) (PPT). Secondary outcome measures, on the other hand, will include differences in cervical range of motion (CROM) and neck disability (ND) after the HILT application in participants with chronic nonspecific NP. The evaluations will be carried out by two independent evaluators: evaluator 1 (PPT and PI) and evaluator 2 (CROM and ND). PPT will be evaluated with algometry at six established bilateral points [24] (Fig. 3), RPI and MPI with numeric pain rating scale (NPRS) [31], cervical ROM with an inclinometer (CROM device) [32–34], and neck disability (ND) through the neck disability index (NDI) [35, 36]. The evaluations of the outcome measures of interest will be carried out in three instances: pretreatment (T0: baseline), the fourth week (T2: the 8th HILT session, end of treatment), and week 20 (T3: 12 weeks post-treatment or follow-up) (Fig. 2).

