### Interim analyses {21b}

No provisional analyses will be performed. In the event of participant discontinuity, the statistical analysis will employ intention-to-treat principles to ensure a comprehensive and unbiased evaluation of the data.

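### Pain-drug use after entry is listed as an exclusion criterion, and nothing says whether randomised participants who meet it stay in the analysis

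*Protocol article*

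**What the plan says.** All references are to the protocol article.

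- **Eligibility criteria {10}** lists among the exclusions: "Analgesic, anti-inflammatory, or muscle relaxant drugs (either for continuous use or those used during the study". Eligibility is an entry check: "The evaluators will verify whether the patients will be eligible to participate in the study based on patient history and clinical examination". Entry also requires "NP at rest of 3 or greater on a 0 to 10 numerical pain rating scale (NPRS".
- **Relevant concomitant care {11d}** states that "participants will not be allowed to start any other interventions or medications, especially on the days that the evaluations and treatments are carried out". It gives no consequence for someone who does.
- **Provisions for post-trial care {30}** states: "The evaluators will keep an electronic record (in Microsoft Excel) of the medications taken during the week".
- **Criteria for discontinuing {11b}** states: "If people discontinue treatment, the analysis will be by “intention to treat,” recording the reasons for leaving the study".
- **Interim analyses {21b}** says that, if participants discontinue, "the statistical analysis will employ intention-to-treat principles to ensure a comprehensive and unbiased evaluation of the data". The section on non-adherence and missing data {20c} repeats the principle, again for cases of discontinuation.
- **Outcomes {12}** opens: "The main outcomes will be the changes in pain intensity at rest (RPI". Pain on movement and pressure pain threshold are the other main outcomes.

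**The concern.** An eligibility criterion should be decidable before randomisation. Half of this one is not, because it refers to drug use over the four treatment weeks and the twelve weeks to follow-up. People with chronic neck pain who do badly are more likely to reach for these drugs. That is an inference and not a statement in the protocol, but it is a reasonable one. If HILT works, more sham participants would then meet the criterion. The protocol also contradicts itself on whether participants are blinded (yes under Trial design {8}, no under Who will be blinded {17a}), and unblinded participants would make unequal use more plausible.

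If users were taken out, the analysis would select on a consequence of the outcome. It would remove the participants with the worst pain, and more of them from sham, so sham would look better than it is and the treatment difference would shrink. The safeguard one would expect, intention to treat, is tied to discontinuation. It does not clearly reach a participant who takes a drug and attends everything.

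**Working it through.** **Step 1. The sections side by side.** Take a randomised participant who takes one of the listed drugs in week 3 and attends all sessions and assessments.

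- Under {10}, an exclusion criterion is met.
- Under {11d}, a rule is broken, with no stated consequence.
- Under {30}, the use is logged.
- Under {11b}, {21b} and {20c}, nothing is triggered, because the participant has not discontinued.

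One analyst could drop this person under {10} and another could keep them under the general intention-to-treat principle. Neither would be contradicting an explicit sentence about drug users.

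**Step 2. The plan's own sample size, used as the yardstick.** With d = 0.6, alpha 0.05, power 0.80 and 1:1 allocation, a one-sided two-sample t test needs 35.04, so 36 per group, or 72 in total. This matches the protocol, which does not state sidedness (a two-sided test needs 44.6, so 45 per group). Adding 15%: 36 × 1.15 = 41.4, so 42 per group, or 84, also a match. The allowance is therefore 84 − 72 = 12 participants, or 12/84 = 14.3%.

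**Step 3. Effect of dropping users (illustration).** The assumed inputs, not given in the protocol, are:

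- SD 2 points and a true difference of 1.2 points, which is 0.6 SD and equals the planning effect size;
- a latent tendency to use drugs with correlation ρ to pain, with a drug taken when the tendency exceeds a cut-off c;
- c = 0.67 or 1.0, giving 25% or 16% use in sham;
- ρ = 0.2, 0.4 or 0.6;
- no effect of the drugs on pain.

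With a = c + 0.6ρ:

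- use in sham = 1 − Φ(c), and use in HILT = 1 − Φ(a);
- difference among non-users, in SD = 0.6 − ρφ(c)/Φ(c) + ρφ(a)/Φ(a); multiply by 2 for points;
- number retained = 42Φ(c) + 42Φ(a).

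Example, c = 0.67 and ρ = 0.6, so a = 1.03. The sham mean shifts by 0.6 × 0.3187/0.7486 = 0.255 and the HILT mean by 0.6 × 0.2347/0.8485 = 0.166. The difference is 0.6 − 0.255 + 0.166 = 0.511 SD, or 1.02 points. Retained: 42 × 0.749 + 42 × 0.849 = 67.1.

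| c | ρ | Use, sham | Use, HILT | Difference (points) | Attenuation | Retained of 84 |
|---|---|---|---|---|---|---|
| 0.67 | 0.2 | 25.1% | 21.5% | 1.18 | 1.8% | 64.4 |
| 0.67 | 0.4 | 25.1% | 18.1% | 1.12 | 6.9% | 65.8 |
| 0.67 | 0.6 | 25.1% | 15.1% | 1.02 | 14.9% | 67.1 |
| 1.0 | 0.2 | 15.9% | 13.1% | 1.18 | 1.4% | 71.8 |
| 1.0 | 0.4 | 15.9% | 10.7% | 1.14 | 5.4% | 72.8 |
| 1.0 | 0.6 | 15.9% | 8.7% | 1.06 | 11.4% | 73.7 |

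**Step 4. A second model.** This one lets the log-odds of use rise by 0.5 to 1.5 per SD of pain, with 10% to 30% users in sham. Dropping users removes about 5% to 24% of the HILT arm, and the difference falls from 0.60 to between 0.59 and 0.48 SD, an attenuation of about 2% to 20%. The direction is the same and the range is similarly wide.

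**Step 5. What keeping users costs.** If the drugs relieve pain by an assumed 1 to 2 points and use is 25% in sham against 15% in HILT, the difference with everyone kept is 1.2 − 1 × 0.10 = 1.10 down to 1.2 − 2 × 0.10 = 1.00 points.

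**The case against.** The strongest reply is that the protocol never says drug users are removed. Eligibility is checked at entry, so the phrase may be meant to screen out people who take these drugs or expect to need them. If drug use led to withdrawal, that person would have discontinued and intention to treat would apply. If it did not, nobody is removed. The weekly log fits keeping users and recording what they take. The section on adverse events {22} does speak of the exclusion criteria as a means of eliminating participants, but it concerns complications of phototherapy. On this view only an omission is left, and the handling of deviations commonly sits in a full protocol or analysis plan that is not shown.

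Much of this stands. A reader might infer that participants will be removed and that the protocol therefore flatly contradicts intention to treat. The text does not support that, and the conflict is conditional. The omission argument does not stand. A criterion that can be met only after entry is printed among the exclusions, and that is a fault in what the article states.

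The objection on size also has force. A reader could take 12% to 15% as the likely attenuation, but that needs a correlation of 0.6, and weaker links give 1% to 7%. A reader could also compute 36 × 0.75 + 36 × 0.85 = 57.6 and conclude that about 58 remain. That starts from 72, whereas the protocol enrols 84. Finally, Step 5 shows that keeping users can dilute the difference about as much as dropping them. The gain from keeping them is an intact randomised comparison, and not necessarily a larger estimate.

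**Conclusion.** The point holds in a conditional form. The protocol lists as an exclusion criterion an event that can occur only after randomisation and is plausibly linked to pain, and no section says whether drug users who do not discontinue stay in the analysis. Applied as written, the criterion could exclude participants selectively by arm, against the intention-to-treat principle stated elsewhere.

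The size is uncertain and rests wholly on assumed inputs for SD, drug use and its link to pain. Across the cases in the Step 3 table the bias is toward no effect and ranges from trivial to moderate. In four of the six cases fewer than the calculated 72 remain even with no other losses; in the other two a margin of about one or two participants is left. The case for change rests on the ambiguity and the low cost of removing it, and not on any single figure.

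**What to change.** Reconcile {10}, {11b}, {11d}, {30}, {21b} and {20c}:

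1. State that the drug criterion decides eligibility only, as judged at enrolment.
2. State that every randomised participant stays in the primary analysis whatever is taken later, whether or not they discontinue.
3. Leave the rule on medication during the trial in {11d} to the investigators. Only its consequence for the analysis needs stating.
4. Report drug use by arm and assessment period from the weekly log already kept.
5. Add one sensitivity analysis that sets pain values after drug use to missing, fitted in whatever primary model is used. The article names a two-factor ANOVA or Kruskal–Wallis test, so how that model would handle the missing values must be stated.

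The cost is a few sentences and one extra analysis, with no new data collection. The downside is that the primary estimate then includes the effect of any drug use, which may itself dilute the difference. The report by arm lets readers judge how much.

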### Who will take informed consent? {26a}

All patients included in the study must validate their participation by signing an informed consent with the evaluator’s prior explanation.

### Additional consent provisions for collection and use of participant data and biological specimens {26b}

N/A. Not applicable for this study.

## Interventions

### Explanation for the choice of comparators {6b}

HILT’s studies on CNNP are limited and done without using a placebo control. In this study, HILT will be compared with a sham HILT application. Placebo comparators are considered the gold standard for evaluating the efficacy of an intervention in clinical trials. This will allow assessing the analgesic efficacy of HILT as well as its effect on other variables like cervical ROM and neck disability.

